# STUDY OBJECTIVES

- 1. **Primary Objective**

Does remote IPC modify the global plasma proteomic and mitochondrial response in patients undergoing congenital heart surgery?

**Hypothesis:**

Remote IPC induces significant changes to global proteomic response in plasma and the metabolic function in heart muscle and lymphocyte mitochondria of patients undergoing congenital heart surgery.

**Aim:**

To assess the impact of remote IPC on the global proteomic and mitochondrial metabolic function response to heart surgery with CPB support.

- 1. **Secondary Objectives**

Does remote IPC modify clinical markers of injury and cardiopulmonary function post-CPB in patients undergoing congenital heart surgery?

**Hypothesis:**

Remote IPC reduces post-CPB release of markers of cellular injury and permits recovery of cardiac pump function with less complication including inotrope requirement in patients undergoing congenital heart surgery.

**Aim:**

To assess the impact of remote IPC on lactate release, inotrope requirement, and standard clinical cardiopulmonary assessments in response to heart surgery with CPB support.

# STUDY DESIGN

- 1. **Type of Study**

Small randomised, blinded, surgical trial of preoperative therapy with highly regulated, brief, non-invasively-induced, localised leg ischaemia and reperfusion, for its capacity to invoke remote ischemic preconditioning-related molecular signalling in blood and heart muscle.

- 1. **Number of Subjects**

N=40 Total.

- 1. **Expected Duration of Study**

March 2010-March2012

- 1. **Primary and Secondary Outcome Measures**

**Primary outcome measures:** The identification of molecular signalling in blood and heart muscle in response to RIPC induced by highly regulated, non-invasively-induced, localised leg ischaemia (5min) and reperfusion (5min) for 4 cycles.

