**5.1.5 Blood sampling**

The following 5 blood samples (6.5 ml each) will be taken from the arterial line that is routinely placed in all patients: baseline, immediately after discontinuation of CPB, at 6, 12, and 24 hours following discontinuation of CPB. No additional lines or invasive procedures will be performed apart from those that routinely required for heart surgery. From each sample, 1.5 ml will be used for proteomic assays, and 5 ml for the lymphocyte mitochondrial function assays.

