**8.1.4. Gel Data Analysis**

Data obtained from the gels will be quantified using the DeCyder version 6.5 software (GE Healthcare). The Differential In-gel analysis (DIA) will be used to optimize spot detection, with the master gel being assigned automatically to the gels with most spots detected. The Biological Variation Analysis (BVA) module will be used for analysis of each sample according to the corresponding age-group. The filtering parameters will then be set to determine the spots that: had a p-value ≤ 0.05 for the t-test employed to test the variation between age-groups and a >1.5 fold change in abundance between the groups.

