**8.1.5. Spot Excision and Identification**

Proteins of interest (determined by change from baseline) will be excised robotically using the Ettan Spot-picker (GE Healthcare) and identified by tandem mass spectrometry (MS/MS) on an HPLC-Chip ESI-Trap XCT tandem mass spectrometer or LTQ-FT mass spectrometer. Protein identification will be verified with the use of western blots using specific antibodies.

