**8.2 Assessment of Mitochondrial Function (myocardial & lymphocyte)**

Ischemia-reperfusion injury diminishes: mito complex I and IV activities, limits maximal O2 consumption capacity and the efficiency of mito O2 consumption, including greater propensity for the loss of mitochondrial membrane potential (36). Thus the strategy to assess evidence for cardioprotection induced by IPC protocol will be to measure the integrity of mitochondrial respiratory chain enzymes; their activity rates as well as the activation of upstream signalling protein kinases. As our laboratory has long experience in miniaturised metabolic assays for very small clinical samples of tissue and blood (with aid of highly sensitive Cary 300 and Nanodrop spectrophotometers) a number of concurrent assays are permissible in each sample.

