# STATISTICAL METHODS

**10.1 Sample Size Estimation**

Sample size is based primarily on the successful study of RIPC in children (see ref 17) where n=approximately 20 per treatment group. This prior study was amply powered to detect differences in clinical and molecular measures. Notably, post-operative inotrope usage was greatly diminished by RIPC. Based on these inotrope usage results, a power of 0.8, alpha=0.05 and sigma of 3.9 indicates that a sample size of n=20 was required. Injury was deemed to be diminished by RIPC on the basis of reduced troponin I release, thus for a power of 0.8, alpha of 0.05 and a sigma of 3 the sample size required is calculated as n=16. Based on our laboratory’s ability to detect a 20% difference in mitochondrial oxygen consumption in human tissue preparations at least 10 subjects are required to detect this difference (power=0.8, sigma=14.5, alpha=0.05, 2 groups. Similarly, the detection of changes in many mitochondrial proteins measured by proteomic assays, are also quite sensitive ranging between 10-20%. Thus a sample size of n=20 per group will yield ample statistical power.

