**10.3 Statistical Analysis Plan**

Lab Assay analyses will be performed on coded samples by Drs [name] and [name] and the values then made available for statistical testing when all tests are complete. Statistical analyses will be performed by Drs [name], [name] & [name]. An independent professional statistician experienced in trials will be employed to check and verify the analyses prior to and after breaking the blinding. In addition to two-way ANOVA or unpaired t test, statistical analysis will employ stepwise multivariate regression and analysis of covariance tests in order to determine potential influence of age, gender, bypass time, drugs, body weight and other morphometric and clinical factors.

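### The primary outcome names no variable, tissue, time point, contrast or success criterion, so the protocol does not prevent a primary claim from any one of many unadjusted assays

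*Protocol*

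**What the plan says.** Section 3.1 poses a yes/no question, and its hypothesis predicts an effect in three compartments: "Remote IPC induces significant changes to global proteomic response in plasma and the metabolic function in heart muscle and lymphocyte mitochondria". Section 4.4 gives the primary outcome as "The identification of molecular signalling in blood and heart muscle in response to RIPC", followed only by a description of the cuff cycles.

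The sections that might fill the gap do not:

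- **Assays (8.1, 8.2).** Plasma is profiled on 2D gels. Myocardium and lymphocytes go to oxygen consumption, complex activities, pore opening, phosphoproteins, apoptosis and electron microscopy. Section 8.2 notes that "a number of concurrent assays are permissible in each sample". None is singled out.
- **Times (5.1.5).** Blood is drawn at "baseline, immediately after discontinuation of CPB, at 6, 12, and 24 hours following discontinuation of CPB". None is primary.
- **Gel criterion (8.1.4, 8.1.5).** Spots are kept if they "had a p-value ≤ 0.05 for the t-test employed to test the variation between age-groups and a >1.5 fold change in abundance". The contrast is worded for age, not treatment. The next section selects on another basis: "Proteins of interest (determined by change from baseline) will be excised robotically".
- **Sample size (10.1).** The argument rests on inotrope use, which is a secondary outcome, on troponin I, which is in neither outcome list of section 4.4, and on mitochondrial oxygen consumption, for which "at least 10 subjects are required to detect this difference". None is called primary.
- **Analysis (10.3).** "In addition to two-way ANOVA or unpaired t test, statistical analysis will employ stepwise multivariate regression and analysis of covariance tests". No primary test is identified.

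**The concern.** A randomised trial with a hypothesis of significant change needs one result, fixed in advance, on which that hypothesis stands or falls. Here the outcome describes a research activity, identifying signalling, and not a quantity compared between groups. Many assay results could be put forward as the primary finding, and nothing in the protocol limits the choice to one made before unblinding. The false-positive rate of the primary claim is then undefined, and a reader of the report could not tell a planned result from a selected one. Controlling the gel spots alone would not cure this, because the mitochondrial and signalling assays would remain open.

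**Working it through.** **1. Reproduce the plan's own molecular figure (section 10.1).** Inputs: difference 20%, sigma 14.5, alpha 0.05, power 0.80, two groups. I assume that sigma is in the same percent units, that the test is two-sided and that the 10 is per group.

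- Standardised difference: 20 / 14.5 = 1.379.
- Two-sample t test, power 0.80: 9.3, rounded up to 10 per group. The stated figure reproduces.
- Power is 0.83 at 10 per group and 0.99 at the planned 20 per group.
- Smallest difference detectable with power 0.80 at 20 per group: 0.909 × 14.5 = 13.2%.

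The other two calculations cannot be reproduced, because no difference is stated. Read as per-group sizes with a two-sided t test, inotrope use (sigma 3.9, n = 20) implies a difference of about 3.5, and troponin I (sigma 3, n = 16) about 3.1.

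**2. Count the candidates.** The protocol gives no total, so these are my counts.

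- Assay families: proteomics (8.1) plus 8.2.2 to 8.2.7, which is 1 + 6 = 7.
- Readouts in 8.2.2 to 8.2.5: oxygen consumption 6 (State III, State IV, maximal, complex I, complex III, ADP:O), complex activities 4, pore opening 2 (membrane potential, swelling), phosphoproteins 3. Total 6 + 4 + 2 + 3 = 15.

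**3. False-positive chance if any one test at 0.05 were taken as success.** For k independent null tests it is 1 − 0.95^k. The last column is a simulation of 4,000 null trials with 20 per group and equal correlation 0.5 between outcomes.

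| k | Independent | Correlation 0.5 |
| --- | --- | --- |
| 5 | 22.6% | not run |
| 7 | 30.2% | about 24% |
| 15 | 53.7% | not run |
| 20 | 64.2% | about 42% |

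At correlation 0.8 the simulated rates are about 15% (k = 7) and 23% (k = 20).

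**4. Effect of enforcing the *and* in the hypothesis.** Suppose each of the three compartments must show at least one significant result among 10 independent assays.

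- One compartment: 1 − 0.95^10 = 0.401.
- All three, with no effect anywhere: 0.401³ = 0.065, or about 6.5%.
- If two compartments truly respond and pass, the chance of wrongly adding the third is still about 40%.

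**5. Gel spots.** The fold-change filter helps by an amount that depends on spot variability, which the protocol does not give. In simulation at 20 per group, with both conditions required, the false-positive rate per spot is about 0.005% at an assumed CV of 30%, 0.9% at 50% and 3.3% at 70%. With an assumed 500 independent spots, the chance of at least one false spot is about 2.5%, 99% and nearly 100%. The filter therefore cannot be relied on to replace multiplicity control.

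**The case against.** The strongest reply has four parts.

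*No rule says that one assay suffices.* This stands. A reader might infer that any single assay at p < 0.05 would confirm the primary hypothesis, or that no result could make the trial negative. The protocol says neither. Its hypothesis joins three compartments with *and*, and a gel spot must also pass a fold-change filter. But neither section 4.4 nor section 10.3 says that all three compartments must be positive, or what counts as positive within one. The gap is the missing rule.

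*The number of tests is uncertain.* This also stands. It is tempting to multiply all readouts by all specimens and reach a rate near 100%. The protocol does not support that. Sections 8.2.4 and 8.2.5 speak of myocardial or lymphocyte material as alternatives, section 8.2.6 concerns leukocytes only, and readouts from one mitochondrial preparation will be correlated.

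*This is a small mechanistic study, and multiplicity belongs in an SAP.* This stands in part. A SAP may well set the model and the adjustment. The primary variable belongs in the protocol, and this protocol does state a primary outcome, in a form that cannot be measured. If the study is meant to be exploratory, it should say so and drop the hypothesis of significant change.

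*Any particular endpoint is a matter of preference.* Largely fair. A reader might take section 10.1 as having already powered State III respiration in right ventricular muscle. It refers only to oxygen consumption by mitochondria from human tissue, without naming the respiration state or the source. The research question also puts the plasma factor first, and the myocardial specimen is small (10-15 mg), is shared between assays and is taken after cardioplegia. The choice is the sponsor's. The need to make one is not affected.

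**Conclusion.** The point holds in this form: the primary outcome is not a measurable endpoint, no other section repairs it, and the protocol leaves a primary claim open to any of many unadjusted assays chosen after the data are seen. If one positive test were accepted, the false-positive chance would be about 23% to 64% for 5 to 20 independent tests, and about 24% to 42% for 7 to 20 tests with correlation 0.5. Requiring all three compartments could bring it to about 6.5% when there is no effect anywhere. These figures show the size of the exposure under assumed test counts and are not the trial's actual error rate, which is undefined without a rule. Sample size is not the obstacle: for the one molecular measure with a stated difference and SD, 20 per group gives power 0.99, provided that sigma is in percent units and applies to the measure chosen. The outcome should be corrected before unblinding, because the meaning of the primary result depends on it.

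**What to change.** 1. In section 4.4, name one primary variable with its tissue, time point and RIPC-versus-sham contrast. Alternatively, name one per compartment and state whether all or any must be significant, with the multiplicity adjustment to match.
2. Mitochondrial oxygen consumption in myocardium is a natural candidate. There is one resected specimen per patient, so no choice of time arises, and it is the only molecular measure with a stated difference and SD in section 10.1. The sponsor must confirm that sigma 14.5 applies to the respiration state and tissue chosen, and say how inadequate specimens will be handled. If several co-primary measures are preferred, a Bonferroni split over 5 tests still leaves power 0.94 for a 20% difference with that sigma.
3. Declare the plasma proteome a separate RIPC-versus-sham objective with false discovery rate control, in place of the unadjusted per-spot threshold. Correct the age-group contrast in section 8.1.4 and reconcile it with the selection rule in section 8.1.5.
4. Label all other assays secondary or exploratory, and name the primary test in section 10.3.

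**Cost.** These are protocol amendments that need no added patients or samples. A positive result in another assay can no longer be called the primary result, and fewer gel spots will be declared. If the single-endpoint route is taken, the sponsor must also accept that part of the present broad question moves out of the primary claim.

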**Secondary outcome measures:**

Alveolar-arterial (A-a) oxygen gradient and lung compliance will be obtained as a part of routine clinical assessment. Measures of lung function oxygenation index and alveolar-arterial oxygen gradient at 3, 6, 12, 24 hours post-op. Measurements including mean systemic arterial, and right atrial pressures are made at 3, 6, 12, and 24 hours after aortic cross clamp release. The doses of inotropic, chronotropic, and afterload reducing agents at the time of the cardiac output measurements are recorded. For between-group comparisons, a total inotrope dose score is calculated by adding the doses of dopamine and dobutamine in micrograms per kilogram per minute and assigning an arbitrary equivalent value of 10µg•kg-1•min-1 inotrope for each 0.1µg•kg-1•min-1 epinephrine. Daily post-operative measurements of arterial blood gases, serum glucose, calcium, electrolytes, hematologic parameters, arterial lactate, blood urea nitrogen, and creatinine, the total volume and type of fluid intake, urine output, and chest tube drainage, the total hours of mechanical ventilation and the days in the CICU and the hospital are recorded.

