# PROTOCOL SYNOPSIS

| Title | The protective effect of remote ischaemic preconditioning in congenital heart disease patients undergoing cardiopulmonary bypass surgery |
| --- | --- |
| Objectives | Support of the circulation during heart surgery using the heart-lung bypass machine is inevitably associated with organ damage and associated reduced function. This is due to reduced blood flow (ischaemia), the effects of restoration of flow (reperfusion injury) and the subsequent inflammation that is caused. The body has its own way of protecting itself against reduced blood flow and oxygen by a mechanism known as preconditioning. In essence, brief periods of mild ischaemia are protective against a subsequent more severe episode of ischaemia. These periods of mild ischaemia can be of the organ itself or of another organ in the body. For example ischaemia of the leg can protect the heart against ischaemia, so called “remote preconditioning”. We have shown in animal and human models that remote preconditioning using a tourniquet placed around a thigh for brief periods (similar in duration to when taking blood samples from children) reduces the amount of injury to heart muscle by 50% and also leads to improved heart and lung function. We have shown that remote preconditioning in a similar way protects the organs of a heterogeneous group of children undergoing cardiac surgery, resulting in better function of the heart and lungs and also a reduction of the inflammatory response to the heart-lung machine. This could potentially reduce the problems in looking after children after surgery and also reduce the amount of time spent in the intensive care unit.  We will study a more uniform group of patients undergoing cardiac surgery in the neonatal period inorder to identify key protein and metabolic changes that occur within this cardioprotective protocol. All interventions will be performed during the period of routine general anaesthesia at the time of surgical repair. We will study the degree of organ injury induced by heart-lung bypass using standard intensive care parameters and equipment for measuring lung function. The degree of heart muscle and blood cell metabolic function will be assessed by laboratory tests. Samples will be taken from routinely discarded resected cardiac tissue and indwelling catheters routinely placed at the time of surgery and not require additional venepuncture. Measurements will be made prior to surgery and also at set time intervals in the first 24 hours postoperatively to determine the evolution of effects. |

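### Several secondary outcomes in section 4.4 have no scheduled pre-operative value although the synopsis promises measurements before surgery; one record before cuff inflation would be a cheap gain in precision

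*Protocol*

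**What the plan says.** The Protocol Synopsis describes the clinical side of the study as follows: "We will study the degree of organ injury induced by heart-lung bypass using standard intensive care parameters and equipment for measuring lung function". It then turns to laboratory tests and to samples from resected tissue and indwelling catheters, and goes on: "Measurements will be made prior to surgery and also at set time intervals in the first 24 hours postoperatively to determine the evolution of effects". That sentence does not say which measurements it means.

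Section 4.4 (secondary outcome measures) sets the times:

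- Oxygenation index and A-a gradient: "Measures of lung function oxygenation index and alveolar-arterial oxygen gradient at 3, 6, 12, 24 hours post-op".
- Pressures: "Measurements including mean systemic arterial, and right atrial pressures are made at 3, 6, 12, and 24 hours after aortic cross clamp release".
- Gases, chemistry and lactate: "Daily post-operative measurements of arterial blood gases, serum glucose, calcium, electrolytes, hematologic parameters, arterial lactate, blood urea nitrogen, and creatinine".
- Compliance: "Alveolar-arterial (A-a) oxygen gradient and lung compliance will be obtained as a part of routine clinical assessment", with no time point.

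The only scheduled baseline is the research blood in section 5.1.5. Each 6.5 ml sample is divided there into 1.5 ml for proteomics and 5 ml for lymphocyte mitochondrial assays. Section 10.3 plans ANCOVA and stepwise regression on age, gender, bypass time, drugs, body weight and other clinical factors. It does not name an outcome's own pre-operative value.

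**The concern.** The secondary aim (section 3.2) is to assess lactate release and cardiopulmonary function in response to surgery, and the synopsis wants to show how effects evolve. With the section 4.4 schedule, neither can be expressed relative to the child's state before treatment for lung function, pressures, gases, lactate or creatinine.

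The trial has 20 children per arm, aged one month to 18 years, with unstratified allocation. Differences between children that exist before bypass will therefore form part of the post-operative variation. A pre-treatment value of the same variable is usually a cheap way to remove some of it. This is a matter of which data are collected: no analysis plan can recover a reading that was never recorded.

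**Working it through.** **Step 1: scheduled times side by side.**

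| Outcome | Before surgery | After surgery |
|---|---|---|
| Oxygenation index, A-a gradient | none | 3, 6, 12, 24 h |
| Arterial and right atrial pressure | none | 3, 6, 12, 24 h after clamp release |
| Gases, lactate, creatinine, chemistry | none | daily |
| Lung compliance | no time given | no time given |
| Proteomics, lymphocyte mitochondria | baseline sample | end of CPB, 6, 12, 24 h |
| Inotrope score, ventilation hours, chest drainage, CICU and hospital days | no natural baseline | recorded |

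The baseline blood volume is fully used (1.5 + 5 = 6.5 ml), so section 5.1.5 does not supply a baseline lactate, gas or creatinine. The gap covers the first three rows, and row four is untimed.

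**Step 2: the plan's own figure.** Section 10.1 has one sample-size calculation with all inputs stated: a 20% difference in mitochondrial oxygen consumption, sigma 14.5 (read as percentage points), alpha 0.05 (taken as two-sided) and power 0.8.

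n per group = 2 × (1.960 + 0.842)² × (14.5/20)² = 2 × 7.85 × 0.5256 = 8.25, rounded up to 9. The t-based version gives 9.3, rounded up to 10, as stated. This is an unadjusted two-group formula. The inotrope and troponin calculations state no difference, so they cannot be reproduced, and they mention no baseline adjustment either. No stated power therefore depends on a baseline.

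**Step 3: what a baseline could be worth.** Inputs: n = 20 per arm (section 5.1.1), and an assumed correlation r between pre-treatment and post-operative value.

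- Variance factor under ANCOVA: 1 − r².
- Equivalent n per arm: 20/(1 − r²).
- Difference detectable with 80% power, unadjusted: (1.960 + 0.842) × √(2/20) = 0.886 SD; adjusted: 0.886 × √(1 − r²).
- Allowance for the lost degree of freedom: multiply the variance by 1 + 1/(40 − 2 − 2) = 1.028.

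| r | 1 − r² | Equivalent n per arm | Detectable difference (SD) | Power for 0.886 SD | Variance factor with df allowance |
|---|---|---|---|---|---|
| 0 (unadjusted) | 1 | 20 | 0.886 | 80% | not applicable |
| 0.1 | 0.99 | 20.2 | 0.881 | 80.4% | 1.017 |
| 0.2 | 0.96 | 20.8 | 0.868 | 81.6% | 0.987 |
| 0.3 | 0.91 | 22.0 | 0.845 | 83.6% | 0.935 |
| 0.5 | 0.75 | 26.7 | 0.767 | 89.9% | 0.771 |
| 0.7 | 0.51 | 39.2 | 0.633 | 97.5% | 0.524 |

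Only the last column includes the degree-of-freedom allowance. At r = 0.1 that factor exceeds 1, so adjustment costs slightly more than it gains; at 0.2 the gain is about 1%.

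**Step 4: the comparator.** The table compares with an unadjusted test. Section 10.3 already adjusts for age and weight. Where compliance or creatinine follows age and size, what counts is the correlation left after those covariates, which is probably lower than r.

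**The case against.** - **The synopsis sentence may mean only the samples.** It names no variables and directly follows the sentence on tissue and catheter samples. Read that way, section 5.1.5 delivers it. This stands: a reader might infer that section 4.4 flatly contradicts the synopsis, but the text supports only a mismatch to be reconciled. The schedule in 4.4 lacks a pre-operative time on either reading.
- **Not every clinical outcome is affected.** Inotrope score, ventilation hours, chest drainage and length of stay arise only after surgery and lose nothing. Inotrope use is also the clinical outcome behind the n = 20 calculation. This stands.
- **Randomisation protects the comparison.** A reader might infer that chance imbalance before bypass could pass for an effect of RIPC. The post-operative comparison is unbiased without a baseline, and its standard error already allows for chance imbalance. This stands; the loss is precision only.
- **The size is assumed.** The protocol gives no correlations, the gain after age and weight is unknown, and it may be small for oxygen gradients if the unrepaired defect dominates the pre-operative value. This stands.
- **Covariates belong in an analysis plan.** Not naming them in the protocol is no fault. Not scheduling the reading is a matter for the protocol.
- **A true baseline may be hard to take.** Section 5.1.2 starts the cuff cycles straight after induction, while central lines are going in. Right atrial pressure may not be readable before the first inflation. Adjusting for a value taken during or after RIPC could remove part of the treatment effect. This stands and limits the remedy.

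**Conclusion.** The point holds as a low-cost improvement, not as an error that threatens the trial. Oxygenation index, A-a gradient, pressures, blood gases, lactate and creatinine have no scheduled pre-treatment value, and compliance has no time. These outcomes can be neither adjusted for their own starting value nor shown as a change from it.

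Against an unadjusted test, 20 per arm would be worth about 22, 27 or 39 at r = 0.3, 0.5 or 0.7. That rests on assumed correlations and is probably an upper guide, given the covariates already planned. Below about 0.2 there is no useful gain.

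A reader might infer that the trial is underpowered or its results biased for want of a baseline. The documents do not support this: no stated sample size relies on baseline adjustment, allocation is random, and the primary blood measures have a baseline sample.

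**What to change.** Reconcile the synopsis with section 4.4:

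- **Section 4.4:** add one record taken before the first cuff inflation, from values routinely available: arterial pressure, blood gas with A-a gradient and oxygenation index, lactate, ventilator compliance, and the latest pre-operative creatinine. It can be tied to the baseline arterial sample if that is drawn before inflation, which section 5.1.5 does not say. Give compliance post-operative times as well.
- **Right atrial pressure:** include it only if it is read before inflation. Never treat a value taken during or after RIPC as a baseline; record it as missing.
- **Section 10.3:** compare each of these outcomes between arms by ANCOVA with its own pre-inflation value, alongside the covariates already planned.
- **Synopsis:** name the variables measured before surgery. If the sponsor does not want the extra record, limit the sentence to the blood samples.

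The cost is a few fields copied from routine records and a sentence in 10.3, with one degree of freedom per model and some missing baseline readings.
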